### 3. Protocol Synopsis

|                           |                                                                                                                                                                                                                                                                                                                                                                                                                                                                                                                                                                                                                                          |
|---------------------------|------------------------------------------------------------------------------------------------------------------------------------------------------------------------------------------------------------------------------------------------------------------------------------------------------------------------------------------------------------------------------------------------------------------------------------------------------------------------------------------------------------------------------------------------------------------------------------------------------------------------------------------|
| Study Title        | Clinical efficacy evaluation of a computer-aided colonoscopy as compared with the standard colonoscopy.                                                                                                                                                                                                                                                                                                                                                                                                                                                                                                                                  |
| Study Design       | A prospective, multi-center, parallel-assigned, two-arm, randomized controlled trial                                                                                                                                                                                                                                                                                                                                                                                                                                                                                                                                                     |
| Study Objective(s) | To evaluate the performance of a computer-aided detection device that is expected to result in non-inferior or improved adenoma detection rate (ADR) when compared with the current standard-of-care procedure.                                                                                                                                                                                                                                                                                                                                                                                                                          |
| Study Population   | 
The target population includes individuals who are undergoing screening, diagnostic, or surveillance colonoscopy.
 
Main inclusion criteria:
 

(1) Age of <math>\geq 40</math> years and <math>< 80</math> years

(2) Subjects who have given signed informed consent form

(3) Informed consensus has been obtained that endoscopic resection should be performed if a lesion is found

(4) Subjects who are scheduled for screening or diagnostic colonoscopy for colorectal cancer (CRC) or surveillance colonoscopy for post-polypectomy follow-up

 |
| Study Endpoints    | 
Primary endpoint:
 

● ADR

 
Secondary endpoints:
 

● Polyp detection rate (PDR)

● Adenomas per colonoscopy (APC)

● Polyps per colonoscopy (PPC)

● Non-neoplastic polypectomy rate (NNPR)

● Sessile serrated lesions per colonoscopy (SPC)

● Advanced adenomas per colonoscopy (AAPC)

● Withdrawal time

                                                                                                                                                                           |
| Duration of Study  | The study will include a Screening Visit (1 day) and an Intervention Visit (1 day) for colonoscopy.                                                                                                                                                                                                                                                                                                                                                                                                                                                                                                                                      |

|                             |                                                                                                                                                                                                                                                                                                                                                                                                                                                                                                                                                                                                                                                                                                                                                                                                                               |
|-----------------------------|-------------------------------------------------------------------------------------------------------------------------------------------------------------------------------------------------------------------------------------------------------------------------------------------------------------------------------------------------------------------------------------------------------------------------------------------------------------------------------------------------------------------------------------------------------------------------------------------------------------------------------------------------------------------------------------------------------------------------------------------------------------------------------------------------------------------------------|
| Statistical Analysis | 
The primary analysis will be the comparison of ADR between an AI-aided colonoscopy and the standard colonoscopy. Differences in ADR between two arms will be expressed as relative risk (RR) with 95% CIs. Non-inferiority will be met for the primary endpoint (ADR) if the lower 2-sided 95% confidence interval (CI) excludes a 10% or greater difference in favor of the control group. The 10% non-inferiority margin reflects a typical maximum clinically acceptable difference for comparative studies. If non-inferiority is demonstrated for the primary endpoint, the endpoint will be assessed for superiority (one-sided p value <0.025) using the Fisher exact test.
                                                                                                                                  |
| Sample Size          | 
The sample size is calculated based on the evaluation of primary outcome ADR. Based on the results of meta-analysis, an expected ADR ranges from around 20% to 40% for computer-aided colonoscopy and SC. A sample size ranging from 198 to 297 per arm is required to establish non-inferiority with a non-inferiority margin of 10%, power of 80% and an alpha level of 2.5% (one-sided). Considering a withdrawal rate of 10% due to potential exclusions and drop-outs, the enrollment goal is 220 to 330 subjects per arm.
 
However, interim analysis of this study performed in October 2022 showed that the ADR in our SC group is 43%, which is significantly higher than the ADR results acquired from meta-analysis (around 20%); therefore, the enrollment goal is increased to 400 subjects per arm.
 |

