## 8. Statistical Analysis

## 8.1. Sample Size Estimation

The sample size is calculated based on the evaluation of primary outcome ADR. Based on the results of meta-analysis, an expected ADR ranges from around 20% to 40% for AI-aided colonoscopy and SC ([Barua et al., 2021](#); [Hassan et al., 2021](#); [Mohan et al., 2020](#); [Shaukat et al., 2021](#); [Spadaccini et al., 2021](#)). A sample size ranging from 198 to 297 per arm is required to establish non-inferiority with a non-inferiority margin of 10%, power of 80% and an alpha level of 2.5% (one-sided). Considering a withdrawal rate of 10% due to potential exclusions and drop-outs, the enrollment goal is 220 to 330 subjects per arm.

However, interim analysis of this study in March 2023 showed that the ADR in our SC group is 49%, which is significantly higher than the ADR results acquired from meta-analysis (around 20%); therefore, the enrollment goal is increased to 750 subjects per arm. (i.e., 1500 subjects in total. )

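### The protocol gives two enrolment goals, 400 per arm in the synopsis and 750 per arm in Section 8.1, and does not say which is in force

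*Protocol*

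**What the plan says.** The synopsis and Section 8.1 open with essentially the same calculation. Planning ADRs run from about 20% to 40% in both arms. The requirement is 198 to 297 evaluable subjects per arm, "A sample size ranging from 198 to 297 per arm is required to establish non-inferiority", at a 10% margin, 80% power and one-sided 2.5%. A 10% withdrawal allowance brings this to 220 to 330 enrolled per arm.

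The two places then part:

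- **Section 3, Protocol Synopsis (Sample Size):** "interim analysis of this study performed in October 2022 showed that the ADR in our SC group is 43" per cent, and "therefore, the enrollment goal is increased to 400 subjects per arm".
- **Section 8.1, Sample Size Estimation:** "interim analysis of this study in March 2023 showed that the ADR in our SC group is 49" per cent, and "therefore, the enrollment goal is increased to 750 subjects per arm. (i.e., 1500 subjects in total".

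Each goes straight from 220 to 330 per arm to its own revised goal. Section 8.1 mentions neither the October 2022 look nor a goal of 400. The synopsis mentions neither the March 2023 look nor a goal of 750.

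**The concern.** The enrolment goal fixes when the confirmatory analysis is done, so it has to be a single number. Here the interim date, the interim ADR and the goal all differ between two parts of the same document. Neither part is a change log, and both sentences are complete, so redaction or text extraction does not explain the difference.

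Both revisions quote the ADR of the SC arm, so the data had been split by arm at least twice. The operators and site investigators know the assignment (Section 7.3.4). In that setting the document should leave no doubt about the final sample size. If the synopsis figure were used, the trial would also fall short of the power that the protocol sets for itself.

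**Working it through.** **Inputs.** From the synopsis and Section 8.1: margin 10% (taken as 10 percentage points), one-sided alpha 2.5%, power 80%, withdrawal 10%, SC ADR 43% or 49%, goals of 400 or 750 per arm. From Section 7.1: 1:1 allocation. Assumption: the true ADR is the same in both arms.

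**Formulas.**
- Evaluable per arm: n = (z_alpha + z_beta)² × 2p(1 − p) / 0.10².
- Enrolled per arm: n / 0.9.
- Non-inferiority power: Φ(0.10 / √(2p(1 − p)/n) − 1.96).

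**1. The figures before the interim looks.** At one-sided 2.5%, (1.960 + 0.842)² ≈ 7.849.
- p = 0.20: 7.849 × 0.32 / 0.01 gives 252.
- p = 0.40: 7.849 × 0.48 / 0.01 gives 377.

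The stated 198 and 297 do not reproduce at 2.5%. They reproduce exactly at one-sided 5%. The withdrawal step does reproduce: 198/0.9 = 220 and 297/0.9 = 330. The alpha mismatch is a separate matter, but it means that the calculation preceding the revised goals cannot be used to decide between them.

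**2. What the revised goals should be on the stated inputs.**

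| SC ADR | Evaluable per arm | Enrolled per arm | Goal stated |
|---|---|---|---|
| 43% | 7.849 × 0.4902 / 0.01 → 385 | 385/0.9 → 428 | 400 (synopsis) |
| 49% | 7.849 × 0.4998 / 0.01 → 393 | 393/0.9 → 437 | 750 (Section 8.1) |

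Neither goal follows. Moving the ADR from 43% to 49% adds 437 − 428 = 9 per arm, so the change in ADR cannot account for a rise from 400 to 750.

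**3. What each goal delivers.**

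| Enrolled per arm | Evaluable (× 0.9) | ADR | Non-inferiority power |
|---|---|---|---|
| 400 | 360 | 49% | Φ(0.10/0.03726 − 1.96) = 76.5% |
| 400 | 360 | 43% | Φ(0.10/0.03690 − 1.96) = 77.3% |
| 750 | 675 | 49% | Φ(0.10/0.02721 − 1.96) = 95.7% |

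**4. The gap.** 2 × 750 − 2 × 400 = 1500 − 800 = 700 subjects.

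**5. Could another basis explain 750?** For superiority from 49% at 80% power (two-sided 5%, normal approximation), a 7.5-point difference needs 695 evaluable and 773 enrolled per arm. An 8-point difference needs 610 evaluable and 678 enrolled. So 750 could come from a superiority target between these, but no such difference is stated in the protocol; this is an assumption. Reading the margin as 10% relative gives about 1,635 to 2,313 enrolled per arm, depending on the ADR and the scale used, and matches neither goal.

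**The case against.** The strongest reply is that this is editorial. The looks are dated, March 2023 is the later one, Section 8.1 is the full sample-size section, and it spells out the total. The natural reading is a synopsis that was not updated. That is probably right, and it argues against treating 400 and 750 as two live stopping points. But the document does not confirm it, and the synopsis still states 400 as the goal.

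A reader might infer three stronger things that the protocol does not support.

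- **That this is an open-label trial whose end can be chosen from the data.** Section 7.3.4 blinds subjects and pathologists. The endpoint needs histological confirmation (Section 7.4.1) by pathologists blinded to arm (Section 7.3.6). The trial is operator-unblinded. A data-driven choice of final analysis is a possibility that the wording fails to exclude; nothing shows that it was intended.
- **That the two looks spent type I error.** Each passage reports only the SC ADR. Neither gives a result for the computer-aided arm or a between-arm comparison. What was compared is a separate question that this contradiction does not settle.
- **That 750 is therefore the right number and need only be copied across.** On the stated inputs 437 would suffice at 49%, so copying 750 would repeat a figure whose basis is not shown.

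The power figures can also be challenged: Sections 3 and 8.3 do not state the scale of the margin and express the treatment effect as a relative risk. That limits the power figures. It does not touch the 700-subject gap.

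**Conclusion.** The point holds as an internal contradiction: two current enrolment goals, 800 and 1500 in total, with no statement of which governs. This should be corrected before the sample size is relied on. The gap between the goals needs no assumption.

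The consequence for power does. With an absolute 10-point margin, equal true ADRs of 49%, one-sided 2.5% and 10% withdrawal, the synopsis goal misses the stated 80% by about 3.5 points (76.5%), while the Section 8.1 goal exceeds it by about 15.7 points (95.7%). At the synopsis's own 43%, 400 per arm still falls short, at 77.3%. Arithmetic cannot tell the reader which goal was meant, because neither follows from the stated inputs. Only the sponsor can say.

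**What to change.** 1. The sponsor confirms the goal in force. Section 8.1's 750 per arm, 1500 in total, is the later and more explicit text.
2. State that one figure in the synopsis and in Section 8.1, as the enrolment at which the confirmatory analysis is done.
3. Record both looks, October 2022 (43%) and March 2023 (49%), in Section 8.1. The synopsis need only agree with it.
4. Give the basis for the figure in Section 8.1: the hypothesis it serves, the assumed ADR in each arm, the scale of the margin, alpha, power and withdrawal. If 750 rests on superiority, state the difference assumed.

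The cost is protocol wording, plus setting out the calculation behind the confirmed goal. If the sponsor confirms 750, the Section 8.1 goal itself does not change.

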## **4. Device Description**

### **4.1. Overall Description**

The investigational medical device is intended to automatically detect potential polyps via colonoscopy in real-time during colonoscopy examinations.

The subject device contains an artificial intelligence/machine learning (AI/ML) advanced algorithm to aid the endoscopists in detection of colonic mucosal lesions and the detected polyps will be highlighted to the endoscopists during the real-time colonoscopy procedures.

### **4.2. Intended Use**

The investigational medical device is intended to be used by qualified endoscopists during colonoscopic examinations to aid detection of colonic mucosal lesions. The target population is adults aged at least 20 years, but not those with a history of colorectal surgeries, with a contraindication to colonoscopy, or pregnancy.

### **4.3. Contraindications**

- (1) Pregnant patients.
- (2) Patients with lower gastrointestinal hemorrhage.
- (3) Patients who had received colorectal surgeries.

### **4.4. Analytical Performance**

The standalone algorithm testing has demonstrated that the investigational medical device could achieve a recall of 93.3% and a precision of 92.6% in poly detection using 9098 images from two study sites (Cathay General Hospital in Taiwan: 3122 images; National Taiwan University Hospital: 5976 images) in Taiwan.

### **4.5. Market Access**

The investigational medical device has been submitted to the local health authority (Taiwan FDA) in May 2021 for market approval and is currently under review.

## 5. Study Rationale

Colonoscopy is clinically used as the gold standard for detection of colorectal cancer (CRC) and removal of adenomatous polyps of the colon and rectum. Evidence has shown that CRC could be prevented by colonoscopic removal of adenomatous polyps. Despite the success of colonoscopy in reducing cancer-related deaths, there exists a disappointing level of adenomas missed at colonoscopy ([Shaukat et al., 2021](#)). In recent years, emerging artificial intelligence (AI) and computer-aided detection (CADe) technology has been shown to improve ADR ([Barua et al., 2021](#); [Hassan et al., 2021](#); [Mohan et al., 2020](#); [Shaukat et al., 2021](#); [Spadaccini et al., 2021](#)). Based on a meta-analysis, ADR was demonstrated to be significantly higher in the CADe groups than in the standard colonoscopy groups, representing a relative risk of 25.2%.

In this study, performance of colonoscopy with or without aid of CADe will be compared in terms of quality indicators. The adenoma detection rate (ADR), which is the proportion of average-risk patients undergoing screening colonoscopy in whom an adenoma is found, is regarded as a robust measure of colonoscopy performance quality that correlates with subsequent cancer risk ([Shaukat et al., 2021](#)). Thus, ADR is taken as the primary outcome of this study. The target population includes individuals who are undergoing screening, diagnostic, or surveillance colonoscopy.

## **6. Objectives**

The goal of this study is to evaluate the performance of a CAdE device that is expected to result in non-inferior or improved ADR when compared with the current standard-of-care procedure.

The main objective of this study is to compare the ADR between a computer-aided colonoscopy (CC) and standard colonoscopy (SC) in human subjects undergoing screening, diagnostic, or surveillance colonoscopy.

## **7. Study Design**

### **7.1. Study Structure**

This study is a prospective, multi-center, parallel-assigned, two-arm, randomized controlled trial. Eligible subjects will be randomly assigned into CC or SC groups in a 1:1 ratio.

### **7.2. Study Population**

#### ***7.2.1. Inclusion criteria***

- (1) Age of  $\geq 40$  years and  $< 80$  years
- (2) Subjects who have given a signed informed consent form
- (3) Informed consensus has been obtained that endoscopic resection should be performed if a lesion is found
- (4) Subjects who are scheduled for screening or diagnostic colonoscopy for colorectal cancer (CRC) or surveillance colonoscopy for post-polypectomy follow-up

#### ***7.2.2. Exclusion criteria***

- (1) Subjects with any of the following prior history or current conditions:
  - a. Contraindications to colonoscopy
  - b. Inflammatory bowel disease (IBD)
  - c. Colorectal cancer (CRC)
  - d. Familial adenomatous polyposis (FAP)
  - e. Colonic stenosis
  - f. Severe organ failure (cirrhosis of Child C, heart failure of ACC / AHA stage D)
  - g. Active gastrointestinal (GI) Bleeding
  - h. Pregnancy
  - i. Prior colorectal surgery, including colonic or rectal resection (except for appendectomy, surgery on the anus, and polypectomy)
  - j. Undergo colonoscopy within 3 years
- (2) Subjects with any of the following conditions per the investigator's judgement:
  - a. High suspicion of IBD, CRC, and FAP.
  - b. High risk of bleeding after endoscopic treatment, and difficult management of anticoagulation or antiplatelet medication.

### **7.3. Study Procedures**

#### ***7.3.1. Screening (Screening Visit)***

- (1) Subjects who are scheduled for either screening colonoscopy, diagnostic

colonoscopy, or surveillance colonoscopy) due to prior history of colon polyps found during colonoscopy done 3 or more than 3 years previously will be asked if they are interested in participating in the study.

- (2) Subjects who are interested will be explained the study details and provided with the informed consent form (ICF).
- (3) After clear understanding of the study and signing the ICF, subjects will be checked for eligibility (inclusion and exclusion criteria), which will be recorded on the case report forms (CRFs).

### **7.3.2. Enrollment**

Eligible subjects based on the inclusion and exclusion criteria will be enrolled in this study and relevant information will be recorded on the CRF.

### **7.3.3. Randomization**

Before colonoscopy initiation, eligible subjects will be randomized in a 1:1 ratio to receive CC or SC.

Randomization will be based on a computer-generated randomization list prepared centrally by the sponsor. Randomization will be stratified by gender, age, and colonoscopy indication (screening, diagnostic, or surveillance) of subjects.

### **7.3.4. Blinding**

The subject and the pathologist who performs the histopathological review will be blinded to the received procedure, while the operator will not be blinded to the study arm assigned to the subject. The investigator at each site will be unblinded to the assigned study arm of the subject, but will be blinded to the assigned study arm of the specimens when conducting the histopathological review

### **7.3.5. Colonoscopy Procedures (Intervention Visit)**

- (1) The subjects will undergo standard bowel preparation and routine pre-procedure examination for colonoscopy (standard of care)
- (2) The colonoscopy (CC or SC) will be performed by qualified endoscopists, who are board-certified gastroenterologists or board-certified colorectal surgeons, using the endoscopy video processor specified in Section 7.5.
- (3) During the colonoscopy, real-time video will be recorded.
- (4) All proximal polyps, and polyps  $\geq 0.6$  cm found at sigmoid, rectosigmoid junction, and rectum will be resected for histopathological examination.

